### Safety profile and monitoring

In this study, all AE encountered during the clinical study will be reported on case report forms. In case of a serious adverse event (SAE), the investigator has a legal requirement to inform the coordinating center office within 24 h via the SAE report form. The coordinating center is responsible for the management of the safety reporting according to European regulation and guidelines. All observed AEs will be evaluated and graded according to the CTCAE, version 4.03. All observed SAEs will be discussed by an independent data safety monitoring board.

Patients will be asked to maintain the full dose throughout the treatment period. However, in case of grade 2 or higher toxicity, dose modification as per protocol will be applied and recorded. The dose will be changed according to the potential relationship to study drugs.

The incidence of metformin-related diarrhea in patients with CRC after surgery is unknown and will therefore be closely monitored. Possible dose modifications in the initial weeks of treatment may be envisioned if the incidence of this AE turns out to be high.

A Data and Safety Monitoring Board (DSMB) will review the progress of the clinical trial and monitor participant safety. During their scheduled meetings, the DSMB will review clinical data, and meeting reports or recommendations will be forwarded to the PIs.

### Sample size and power consideration

The sample size is 40 patients per arm, resulting in a total of 160 patients to be enrolled. Results from our previous clinical trial [29] showed a mean change (standard deviation, SD) of the difference between post- and pre- treatment levels in NFκB equal to + 5% (25%) in the placebo arm versus − 13.5% (25%) in the active (allopurinol) arm. This is equivalent to a − 18.5% absolute difference between treatment arms. Table 3 illustrates the hypothesized treatment effects on NFκB change and relative power in each arm, assuming a normal distribution of the change in NFκB with a mean = 5% in the placebo arm, an equal SD = 25% in all arms, and a two sided alpha error = 5%. The primary analysis will have 80% power to detect a synergistic effect in the combination arm, which is equal to 3-fold single drug effects (i.e.: + 5% arm A vs. -55% arm D). The hypothesis of a striking synergistic effect is based on recent preclinical data of the combination of aspirin and metformin on CRC cell lines as well as pancreatic cancer cell lines [19, 20]. The secondary analyses relative to the main drug effects will have 90% power to detect a difference on the change equal to − 18.5%, compared to the placebo arm (i.e.: + 5% arm A vs. − 13.5% arm B or C), which is the same effect we detected in a previous trial with allopurinol [29]. The calculation takes into account a 10% drop-out rate: therefore the minimum number of patients to be analyzed is set to *n* = 144 (36 per arm). The sample size estimate, and relative power calculation, was performed using a simulation approach (10.000 trials) using R-project software.

**Table 3 Tab3:** Hypothesized effect after 1 year of treatment on the primary endpoint

Treatment arm	N	NFκB % change	1-β (power)
Arm A (placebo)	40	+ 5%	–
Arm B (metformin)	40	−13.5%	90%
Arm C (aspirin)	40	-13.5%	90%
Arm D (aspirin+metformin)	40	−55% (~ 3.0-fold the main effects)	80%

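### The stated 90% single-agent power fits 40 analysed per arm; at the 36 per arm left after the stated 10% drop-out it is about 87–88%

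*Protocol article*

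**What the plan says.** All of this is in the protocol article, under Sample size and power consideration.

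- **Enrolment:** 40 patients per arm, 160 in total.
- **Assumptions:** the change in NFκB is normally distributed with mean +5% on placebo, "an equal SD = 25% in all arms", and "two sided alpha error = 5"%. The single-agent effect comes from an earlier allopurinol trial and is a reduction by an "18.5% absolute difference between treatment arms".
- **Single agents:** "The secondary analyses relative to the main drug effects will have 90% power to detect a difference on the change equal to − 18.5"%, illustrated as arm A against arm B or C.
- **Combination:** "The primary analysis will have 80% power to detect a synergistic effect in the combination arm", with arm D at −55%.
- **Drop-out:** "The calculation takes into account a 10% drop-out rate: therefore the minimum number of patients to be analyzed is set to" 144, which is 36 per arm.
- **Table 3** ("Hypothesized effect after 1 year of treatment on the primary endpoint") lists N = 40 for every arm, beside powers of 90%, 90% and 80%. The column is headed only N.
- **Method:** simulation of 10,000 trials in R.

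**The concern.** The drop-out sentence tells the reader that the stated powers already allow for losing one patient in ten. If so, 90% should come out at 36 per arm. Table 3 prints the same 90% beside 40. The two sizes give different powers on the same inputs, so the 90% cannot be exact at both, and the article does not say which size the simulation used.

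What is at stake is how a negative single-agent result is read. If the 90% belongs to 40 per arm, then at the planned minimum the chance of missing an effect as large as that seen with allopurinol is greater than the 10% a reader would assume.

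**Working it through.** **Inputs**, all from the sample size section: single-agent difference δ = 5 − (−13.5) = 18.5 points; SD σ = 25; two-sided α = 0.05; n = 40 enrolled per arm; n = 40 × 0.9 = 36 analysed per arm.

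**Single agent versus placebo.** The standard error is SE = σ√(2/n), and the standardised effect is δ/SE. The normal approximation to power is Φ(δ/SE − 1.96). The t versions use the noncentral t with noncentrality δ/SE, on either 2n − 2 df (two arms) or 4n − 4 df (error variance pooled over four arms).

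First, the article's own figure at n = 40: SE = 25√(2/40) = 5.590, and δ/SE = 3.309.

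Then n = 36: SE = 25√(2/36) = 5.893, and δ/SE = 3.140.

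| Method | n = 40 | n = 36 |
|---|---|---|
| Normal approximation | 91.1% | 88.1% |
| Two-sample t | 90.5% | 87.2% |
| t, four-arm pooled df | 90.8% | 87.7% |
| Simulated t-test, 100,000 trials | 90.6% | 87.3% |

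The 90% is reproduced at 40. At 36 every method falls short, by 1.9 to 2.8 points. Simulation error does not explain the gap: with 10,000 trials the standard error at 90% is √(0.9 × 0.1/10,000) = 0.3 points.

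**What 90% would need.** At 36 per arm, the difference detectable with 90% power is 19.2 points (pooled df) or 19.4 points (two-sample t), against 18.5 stated. At 18.5 points, 90% needs 39 analysed per arm (normal approximation or pooled df) or 40 (two-sample t). With 10% loss these become 39/0.9 → 44 or 40/0.9 → 45 enrolled per arm, that is 176 or 180 in total against 160.

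**Primary interaction.** The contrast at the Table 3 means is D − B − C + A = −55 + 13.5 + 13.5 + 5 = −23, with SE = 25√(4/n).

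- n = 40: SE = 7.906, ratio 2.909, power 82.9% (normal) or 82.4% (t).
- n = 36: SE = 8.333, ratio 2.760, power 78.8% (normal) or 78.3% (t).

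The printed 80% lies between the two, and the value at 36 is within 2 points of it.

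**The case against.** **The numbers of patients do not conflict.** Seeing 40 in Table 3 and 36 in the text, a reader might infer that the article defines the number analysed in two ways. It does not: 40 is the number enrolled, 36 is the minimum number analysed, and 40 × 0.9 = 36. Table 3 never labels its N as analysed. This stands. What is left open is only which n the powers refer to.

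**36 is a floor.** If fewer drop out, power lies between about 87–88% and 90.5–91%. This also stands, but the drop-out sentence presents the loss as already allowed for, so 36 is the size at which the claim has to be tested.

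**The planned analysis is ANCOVA.** Covariates that correlate with the change would raise power. If that correlation is assumed to be 0, 0.1, 0.2, 0.3 or 0.4, normal-approximation power at 36 is 88.1%, 88.4%, 89.3%, 90.8% or 92.9%, so a value between 0.2 and 0.3 would recover 90%. The article's stated inputs include no such gain, so this cannot support the printed figure. It does mean that the 87–88% describes an unadjusted comparison and may understate the power of the adjusted one.

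**A factorial margin has more power.** Comparing 72 with 72 would give about 99% if there were no interaction. The article, however, powers arm B or C against arm A, and the trial is designed around a strong interaction.

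**The primary power.** A reader might infer that the 80% is wrong too because it equals neither 82.4% nor 78.3%. That treats a rounded figure as exact, and the document does not support calling it a separate error.

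**Conclusion.** The statement that the calculation takes drop-out into account is not borne out for the single-agent power. On the stated inputs the 90% belongs to 40 analysed per arm. At 36 it is about 87–88%, so the type II error is about 12–13% rather than 10%. The primary 80% is only marginally missed at 36 (78–79%).

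This rests on a normally distributed change with SD 25 in every arm, a two-sided 5% test, an unadjusted comparison of one single-agent arm with placebo, and exactly 10% loss in each arm. That the simulation used 40 per arm is an inference from the match; the article does not say so.

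Severity is minor. The shortfall is 2 to 3 points, it concerns a secondary analysis, and neither the enrolment target nor the planned analysis has to change because of it.

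**What to change.** State the n behind each power. Any one of these would do:

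1. Label Table 3 as 40 randomised / 36 analysed per arm, and restate the powers at 36: about 87–88% for arm B or C versus placebo and about 78% for the interaction.
2. Keep 90% for the single agents and restate the difference detectable at 36 per arm as about −19.2 to −19.4 points.
3. State that the printed powers assume all 40 per arm are analysed, and remove the sentence that says drop-out is taken into account.

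The cost is one table label and one or two sentences. No extra patients are needed; the stated figures become slightly less favourable.

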### Statistical analysis

The synergistic effect of aspirin + metformin vs. placebo on the primary endpoint will be assessed using a two-way analysis of covariance (ANCOVA). A multivariate linear regression model will be adopted to study the change in the primary endpoint as a function of treatment and potential confounders or effect modifiers, and to adjust for imbalances between treatment arms. The interaction parameter between treatment arms will be primarily estimated and tested.

#### Secondary analyses

Two-way ANCOVA and multivariate linear modeling will also be applied to estimate and test the main effects of aspirin and metformin alone and to test the association between the secondary endpoints and treatment, adjusting for demographical and clinical factors. First and second level interaction effects between treatment and covariates (other biomarkers or demographics/clinical characteristics such as BMI and HOMA index) on primary and secondary endpoints will be tested in each model. The change of highest grade adenoma at baseline to highest grade adenoma after 1 year after randomization (no adenoma vs low/intermediate vs high grade adenoma) will be compared between the aspirin + metformin and placebo arms using a Wilcoxon test.

Gene expression levels will be analyzed using log-transformed normalized gene expression levels according to the following three-tiered approach to investigate:Candidate genes (e.g. *PTGS1* (*COX1*), *PTGS2* (*COX2*), *VEGF*, *TNFα*, *EGFR*, *NFκB*);Candidate pathways (e.g. mTOR signaling - KEGG04150, NFκB signaling - KEGG04064, VEGF signaling - KEGG04370, FoxO signaling - KEGG04068, Regulation of autophagy - KEGG04140);Genome-wide expression profiles.

Comparisons of changes of candidate genetic markers between arms will be assessed using linear regression from NGS data. To assess the pathway effect as part of the genetic analyses, gene-set enrichment analysis and global tests will be used. Models will be adjusted by age and gender. The effect size will be expressed using fold change values. We will visualize the possible subgroups with heat maps using unsupervised clustering. We will use Ingenuity Pathway Analysis (IPA) and Cytoscape for visualizing the results of the pathway analysis. The statistical analyses of genetic data (expression and genetic characterization of adenocarcinoma using NGS) will be performed in collaboration between the Italian and the German PIs. Statistical analyses will be performed using STATA, SAS, R-project, and Bioconductor software packages.

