**Methods/design:**

This is a randomized, placebo-controlled, double-blind, 2 × 2 biomarker trial of aspirin and metformin to test the activity of either agent alone and the potential synergism of their combination on a set of surrogate biomarkers of colorectal carcinogenesis. After surgery, 160 patients with stage I-III CRC are randomly assigned in a four-arm trial to either aspirin (100 mg day), metformin (850 mg *bis in die)*, their combination, or placebo for one year. The primary endpoint biomarker is the change of IHC expression of nuclear factor kappa-B (NFκB) in the unaffected mucosa of proximal and distal colon obtained by multiple biopsies in two paired colonoscopies one year apart. Additional biomarkers will include: 1) the measurement of circulating IL-6, CRP and VEGF; 2) the IHC expression of tissue pS6K, p53, beta-catenin, PI3K; 3) the associations of genetic markers with treatment response as assessed by next generation sequencing of primary tumors; 4) the genomic profile of candidate genes, pathways, and overall genomic patterns in tissue biopsies by genome wide gene expression arrays; and 5) the evaluation of adenoma occurrence at 1 year.

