#### Secondary objectives

Secondary objectives are:

1. To test the effect of treatment with aspirin and metformin, in combination and independently, on the following secondary endpoints:The change in immunohistochemistry (IHC) expression levels of pS6K, p53, β-catenin, PI3K (from unaffected colon biopsy specimens);The change in the circulating biomarkers IL-6, CRP, VEGF, and HOMA index [homeostasis model assessment [fasting blood glucose (mmol/L)*insulin (mU/L) / 22.5];The gene expression levels of candidate genes (PTGS1-COX1, PTGS2-COX2, VEGF, TNFα, EGFR, NFκB), pathways (mTOR signaling - KEGG04150; NFκB signaling - KEGG04064; VEGF signaling – 04370; FoxO signaling KEGG04068; Regulation of autophagy - KEGG04140), and genome-wide expression profile in unaffected colon biopsy tissue.

2. To define the blood and tissue drug levels of metformin, considering the genetic variability of specific membrane-bound drug transporters which may affect metformin pharmacokinetics and tissue distribution.

3. To genetically characterize the primary CRC using next generation sequencing (NGS) on a panel comprising 180 amplicons of 30 genes (including KRAS, BRAF, NRAS, APC, PIK3CA, TP53, CTNNB1 and EGFR) and determine their association with treatment response.

4. To study the treatment tolerability comparing incidence and grade of toxicities (safety endpoint) among arms (categorized using the Common Terminology Criteria for Adverse Events, CTC-AE version 4.03).

5. To study the serum concentrations of thromboxane B2 (TxB2) as a biomarker of treatment adherence to be correlated with biomarker modulation and toxicity.

6. To evaluate the effect of treatment on psychological variables (distress, anxiety, and depression) and cancer-related fatigue and to explore their interactions with treatment on the endpoint biomarkers.

7. To evaluate the occurrence of adenoma (low, intermediate and/or high grade intraepithelial neoplasia) at baseline and 12 months after randomization according to the Vienna classification of gastrointestinal epithelial neoplasia.

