
### Study procedures

An overview of “Visit schedule and assessments” is provided in Table 2.

**Table 2 Tab2:** Visit schedule and assessments

Assessments			Treatment Period				
	Screening^1^	Randomization	Baseline	4 Months	8 Months	12 Months	End of study visit
Informed consent	X						
Inclusion/exclusion criteria	X						
Relevant medical history	X						
Prior medication/therapy of current CRC	X						
Physical exam, vital signs and ECOG performance status	X		X	X	X	X	X
Hematology, biochemistry, and coagulation profile	X^2^		X^2^	X^2^	X^2^	X^2^	
Randomization		X					
Blood collection for biological assessment			X			X	
Blood collection for TxB2/metformin quantification^3^			X	X	X	X	
Feces collection^4^			X			X	
Questionnaires (FACIT, HADS, Distress, IPAQ, and EPIC [4])			X			X	
Colonoscopy and biopsies			X^5^			X^5^	
Adverse events	X^6^		X	X	X	X	X
Concomitant medication			X	X	X	X	
Study treatment supply			X	X	X		
Compliance (via pill count)				X	X	X	

1. Within 28 days after day 1

2. Complete blood count (WBC, white blood cell differential count, RBC, Hb, Ht, MCV, MCH, MCHC, RDW, PLT, and MPV), alanine aminotransferase (ALT), aspartate aminotransferase (AST), creatinine, fasting glucose, triglycerides, and cholesterol. Coagulation profile (coag) includes: (International Normalized Ratio) INR, Activated Partial Thromboplastin Time (APTT), prothrombin time (PT), and fibrinogen. At baseline, hematology, biochemistry, and coagulation profile are not needed if the screening visit is performed within 7 days prior to the baseline visit.

3. TxB2/metformin quantification will be performed at the end of the study

4. Only for Italian patients

5. During the colonoscopies at baseline and at 12 months, the occurrence of adenoma (low, intermediate, and/or high grade intraepithelial neoplasia) as well as the histopathological subtype (e.g. tubular, villous, tubulovillous, sessile serrated, traditional serrated, or hyperplastic) will be determined upon routine histopathological analysis according to local practice (i.e. according to the Vienna classification of gastrointestinal epithelial neoplasia). If at least two adenomas with different grading exist, the highest grade will be considered, e.g. occurrence of two intermediate-grade and one high-grade adenoma would result in a categorization as high-grade

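### The adenoma test ranks change from a pre-treatment grade and compares only two of the four arms, which costs power and fits the stated endpoint, adenoma occurrence, poorly

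*Protocol article*

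**What the plan says.** All places are in the Protocol article.

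- **Secondary analyses** fixes the variable: "The change of highest grade adenoma at baseline to highest grade adenoma after 1 year after randomization". The three ordered levels, the arms and the test follow: "no adenoma vs low/intermediate vs high grade adenoma) will be compared between the aspirin + metformin and placebo arms using a Wilcoxon test".
- The same paragraph says that two-way ANCOVA and linear modelling will be used for the main effects of each drug and "to test the association between the secondary endpoints and treatment, adjusting for demographical and clinical factors". Adenoma is not named there.
- **Secondary objectives**, item 7, reads "To evaluate the occurrence of adenoma (low, intermediate and/or high grade intraepithelial neoplasia) at baseline and 12 months after randomization". The **Abstract** (Methods/design) lists "the evaluation of adenoma occurrence at 1 year". Neither defines a change in grade.
- **Table 2, footnote 5** says that adenoma occurrence and subtype "will be determined upon routine histopathological analysis according to local practice" at both colonoscopies.
- **Baseline** places the first dose on the day after the baseline colonoscopy.
- **Study design** describes a 2 × 2 factorial trial with 40 patients in each of four arms.

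**The concern.** The baseline grade is known before any drug is taken, so it carries no information on treatment effect except as a predictor of the later finding. A change score gives it full weight all the same. This adds variation and produces scores that are hard to read: a patient with an adenoma at 12 months can tie with, or occasionally rank above, a patient who never had one. If adenomas found at baseline are resected, the change does not measure progression of a lesion either.

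The named test also leaves out the metformin-only and aspirin-only arms. The Background cites a metformin-alone effect on adenomas (risk ratio 0.60, 95% CI 0.39–0.92), yet the only test named for adenoma in this factorial trial does not estimate that effect. Adenoma is the lesion endpoint among the biomarkers, so a weak or unclear analysis of it would be a real loss.

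**Working it through.** **1. Figure to reproduce.** There is none. The article gives no adenoma rate, effect or power; its power figures concern NFκB. Taken from the article: 40 × 0.90 = 36 analysed per arm, and a two-sided 5% level (stated for NFκB, assumed here). Adenoma prevalences, the high-grade share and the effect sizes are assumptions, except the cited risk ratio of 0.60.

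**2. What the change score does.** Score none, low/intermediate and high as 0, 1 and 2. The article fixes no scores; the simple difference is the natural reading. Change is month 12 minus baseline.

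| Baseline | none at 12 m | low/int. at 12 m | high at 12 m |
|---|---|---|---|
| none | 0 | +1 | +2 |
| low/int. | −1 | 0 | +1 |
| high | −2 | −1 | 0 |

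Low-to-low and high-to-high tie with adenoma-free at both colonoscopies (0). High-to-low (−1) ranks better than adenoma-free at both.

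**3. How often.** Assume prevalence of 20–40% at each colonoscopy, 15% of adenomas high grade, and 12-month grade independent of baseline grade. With baseline prevalence p, among patients with a 12-month adenoma:

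- Score 0 or better: p × (0.85 + 0.15 × 0.15) = 0.8725p, which is 17% at p = 0.20 and 35% at p = 0.40.
- Score strictly better than 0: p × 0.15 × 0.85 = 0.1275p, which is about 2.5% to 5%.

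High-to-low as a share of all patients at control prevalence runs from 0.20 × 0.15 × 0.20 × 0.85 = 0.5% to 0.40 × 0.15 × 0.40 × 0.85 = 2.0%. In an arm of 36 that is 0.2 to 0.7 patients. Ties are the common problem; the reversal is uncommon.

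**4. Why power is lost.** For a measurement with equal variances σ² and within-patient correlation ρ, the change has variance 2σ²(1 − ρ) and the baseline-adjusted outcome has σ²(1 − ρ²). The ratio is 2/(1 + ρ): 2 at ρ = 0 and 1.33 at ρ = 0.5. This is only a guide for a rank test on an ordinal grade, but it shows why the gap narrows as correlation rises.

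**5. Illustration A: any adenoma, combination against placebo.** Assumed: baseline 30%, placebo 35% at 12 months, odds ratio 0.25, 36 per arm. The Wilcoxon test on change is compared with logistic regression of 12-month adenoma adjusted for baseline. The patient random effect is on the logit scale. Ranges are over repeated simulation runs.

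| Random-effect SD | Change score | Adjusted 12-month |
|---|---|---|
| 0 | 32–36% | 67–68% |
| 1 | 31–34% | 57–62% |
| 2 | 29–31% | 44–47% |

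Under no treatment effect, both methods rejected in 4–5% of trials.

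**6. Illustration B: three grades, combination against placebo.** Assumptions as in step 3, 36 per arm, 20,000 trials per scenario, Wilcoxon test on each variable.

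| Risk ratio | Change in grade | 12-month grade |
|---|---|---|
| 0.36 (0.60 × 0.60) | 12–45% | 36–70% |
| 0.60 | 8–20% | 15–30% |

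**7. Arms.** The named test uses 2 × 40 = 80 of 160 randomised patients (72 of 144 analysed). With a risk ratio of 0.60 per drug, the 12-month grade compared at a factorial margin (72 against 72) has 20%, 30% and 41% power at control prevalences of 20%, 30% and 40%.

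**The case against.** **Validity.** Randomisation protects the Wilcoxon test on change, and the simulation agrees. This stands: nothing here makes a positive result false.

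**Match to the objective.** Objective 7 names both baseline and 12 months, so a change is one way to combine them. It is not a flat contradiction, but occurrence and change in grade remain different quantities, and the Abstract names only occurrence at 1 year.

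**Removal of baseline lesions.** A reader might infer that adenomas found at baseline were taken out, so that every 12-month lesion is new. That is likely, but the text does not say it; a biopsy also goes to histopathology. The scoring problem and the added noise arise either way.

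**Automatic improvement.** A reader might also infer that every patient with a baseline adenoma scores as improved. The table in the working shows otherwise: the score is 0 when the grade is unchanged and +1 for low-to-high.

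**Single-drug arms.** The general ANCOVA sentence could be read to include adenoma as a secondary endpoint, so it would be too strong to say that the plan excludes any single-drug estimate. But the sentence does not name adenoma, a linear model suits a three-level grade poorly, and the paragraph then gives adenoma its own two-arm test. Combination against placebo is also a sensible lead contrast, in line with the primary analysis.

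**Limits of the illustrations.** Illustration A is binary and two-arm, so it measures neither the rank reversal nor the omission of two arms. Its odds ratio of 0.25 is large. At the cited risk ratio of 0.60, power is low by either method.

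**Conclusion.** The point holds as one of power, interpretability and fit to the stated endpoint. The change score subtracts a pre-treatment finding, treats a persistent grade as equal to no adenoma, and in the uncommon high-to-low case ranks a patient with an adenoma above one who is adenoma-free.

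Under the assumed strong effect (odds ratio 0.25), power is about 29–36%, against 44–68% for baseline-adjusted 12-month occurrence. At a risk ratio of 0.60 the comparison is 8–20% against 15–30%. The size rests on assumed prevalences and effects. The direction was the same in every scenario tried.

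The omission of 80 of 160 patients might be read as a matching loss of power for combination against placebo. It is not: in a model with an interaction, the single-drug arms add little to that contrast. What the named test lacks is single-drug estimates, and these would be imprecise at this sample size. The endpoint is secondary and the type I error is valid, so this is a worthwhile improvement and not a threat to the trial's main conclusion.

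**What to change.** Replace the Wilcoxon test on change with a model of the 12-month finding:

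- **Outcome:** highest grade at 12 months in the three stated levels, by proportional-odds regression. If high grade is rare, use any adenoma at 12 months, by logistic regression. With a 30% prevalence and a 15% high-grade share (both assumed), a placebo arm would hold about 36 × 0.30 × 0.15 = 1.6 high-grade cases, so the rule for switching should be set before unblinding.
- **Terms:** aspirin, metformin and their interaction in all four arms, with baseline adenoma grade as covariate.
- **Report:** the contrasts of arm D, arm B and arm C against arm A, with confidence intervals.
- **Text:** use one endpoint definition in the Abstract, objective 7 and Secondary analyses, and state whether adenomas found at baseline were removed, because the meaning of the 12-month finding depends on it.

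The cost is a change of analysis wording. Both colonoscopies and their histology are already scheduled, so no new data are needed.

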### Colonoscopy and pinch biopsies clinical procedures

All enrolled patients will undergo colonoscopy with biopsies at baseline and after 12 months of treatment. Colonic biopsies will be collected both in the right and the left colon (6 specimens per site) in order to study the pharmacokinetic and pharmacodynamic properties of the drugs and to verify if there is a different preventive effect in the right versus left colon according to a different anatomic gradient of mutational status [28]. In patients who received right colectomy, 6 biopsies will be taken at the level of the *cul de sac* and 6 biopsies 2 cm above the third Houston valve. In patients operated for a left-side CRC, 6 biopsies will be collected near the ileo-cecal valve and 6 biopsies 2 cm above the third Houston valve or 2 cm above the anastomosis in patients operated for rectal cancer.

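### The plan does not settle whether mucosal gene expression is analysed as a level or a change, and the covariates it states leave out the patient's own baseline expression, which costs precision

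*Protocol article*

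**What the plan says.** **Endpoint.** In the protocol article, Secondary objectives, item 1, the tissue IHC endpoint is "The change in immunohistochemistry (IHC) expression levels of pS6K, p53, β-catenin, PI3K", and the circulating markers are likewise defined as a change. The third endpoint in the same item is worded differently: "The gene expression levels of candidate genes", followed by pathways and a genome-wide profile. It mentions neither change nor a time point.

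**Model.** Secondary analyses gives this endpoint its own paragraph. It begins "Gene expression levels will be analyzed using log-transformed normalized gene expression levels" and lists three tiers: candidate genes, candidate pathways and genome-wide profiles. It then says "Comparisons of changes of candidate genetic markers between arms will be assessed using linear regression from NGS data". Shortly afterwards it says "Models will be adjusted by age and gender", and effects are to be reported as fold changes. Whether a fold change is between arms or post over pre is not said.

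**General rule.** The same section opens with a rule for all secondary endpoints: two-way ANCOVA and linear modelling "to test the association between the secondary endpoints and treatment, adjusting for demographical and clinical factors".

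**Data.** The section on colonoscopy and biopsies states: "All enrolled patients will undergo colonoscopy with biopsies at baseline and after 12 months of treatment". The Abstract (Methods/design) assigns mucosal expression to genome-wide arrays and sequencing to primary tumours. Secondary objectives, item 3, also ties the NGS gene panel to the primary cancer.

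**The concern.** Two things are fixed badly. First, the analysed quantity is a level in the objective, a level at the start of the analysis paragraph, and a change a little later. The sentence about changes names an assay that, for genes, the article uses on the primary tumour. That tumour has been removed, and no repeat sequencing under treatment is described, so the panel cannot supply a change to compare between arms. Either the sentence concerns something else, or it names the wrong platform.

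Second, the stated covariates omit the one most likely to explain variation in 12-month expression, namely the same patient's expression before treatment. An analyst who follows the wording could legitimately compare 12-month levels, or unadjusted changes, with age and gender as covariates. Either choice leaves avoidable variation in the error term of the aspirin, metformin and interaction contrasts, with a planned minimum of 36 analysed patients per arm.

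**Working it through.** **What the plan computes.** No power, SD or correlation is given for gene expression. The stated powers concern NFκB IHC change only. With 36 per arm and SD 25 (normal approximation, two-sided 5%) they come out close to plan:

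- Interaction contrast: −55 − 2(−13.5) + 5 = −23. SE = 25·√(4/36) = 8.33. Power is 78.8%, against 80% stated.
- Single drug against placebo: difference 18.5. SE = 25·√(2/36) = 5.89. Power is 88.1%, against 90% stated.

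These figures confirm the arithmetic frame but do not bear on the gene-expression model.

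**Inputs for the comparison.** n = 36 per arm (Sample size and power consideration). The correlation r between baseline and 12-month log expression is not in the documents, so it is assumed over 0.2 to 0.8. Where age and gender stay in the model, r is the correlation given those two. Equal SD at both times is assumed.

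**Relative variance of a treatment contrast (12-month levels = 1).** The ratios apply equally to a pairwise and to an interaction contrast.

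- Unadjusted change: 2(1−r)
- 12-month value with baseline as covariate: 1−r²

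The last column takes a pairwise difference that has 80% power on levels, (1.96 + 0.84)·√(2/36) = 0.66 SD, and shows its power under unadjusted change / baseline adjustment.

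| r (assumed) | Change | Baseline-adjusted | SE, adjusted / levels | Power, change / adjusted |
|---|---|---|---|---|
| 0.2 | 1.60 | 0.96 | 0.98 | 60% / 82% |
| 0.3 | 1.40 | 0.91 | 0.95 | 66% / 84% |
| 0.5 | 1.00 | 0.75 | 0.87 | 80% / 90% |
| 0.7 | 0.60 | 0.51 | 0.71 | 95% / 97.5% |
| 0.8 | 0.40 | 0.36 | 0.60 | 99.3% / 99.7% |

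**Ordering.** Levels minus adjusted is 1 − (1−r²) = r². Change minus adjusted is 2(1−r) − (1−r²) = (1−r)². Neither is ever negative. So, apart from one degree of freedom, baseline adjustment is at least as precise as either reading of the current text. Unadjusted change beats levels only when r exceeds 0.5.

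**The case against.** The strongest reply is that this is loose wording in a condensed article. No time point is attached to the levels, and nothing says that baseline biopsies are set aside. The sentence on changes directly follows the three-tier list and makes most sense as expression change in the paired biopsies with the platform mislabelled. The general rule adds demographic and clinical factors for secondary endpoints, and the age-and-gender sentence is not said to be exhaustive. The baseline value is not named as a covariate for the primary endpoint either. A full covariate list normally belongs in the SAP.

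Much of this stands, and it rules out several stronger readings that a reader might infer:

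- *The baseline biopsy drops out of the analysis.* This is an inference, and the sentence on changes points against it, at least for the candidate genes.
- *Adjustment is for age and gender only.* The word *only* is not in the text.
- *Chance baseline differences would bias the fold changes.* In a randomised comparison, 12-month levels give an unbiased effect, and chance imbalance is already covered by the type I error.
- *A definite power loss follows from the plan's own effect size.* The ratio 23/25 = 0.92 SD belongs to NFκB IHC change. It cannot be carried over to log expression, which is a different assay and quantity.

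What the reply does not remove is the conflict over level or change, the platform mismatch, and a covariate set that was stated and omits baseline expression. The sentence on changes reaches candidate markers only, not expressly the pathway or genome-wide tiers. Even there, an unadjusted change is less precise than baseline adjustment for any r below 1.

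**Conclusion.** The point holds as an inconsistency together with an inexpensive gain in precision. It is not an error of validity. The article should say whether gene expression is a level or a change, should name the right assay, and should include baseline expression among the covariates.

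The size depends on an r that the documents do not give. Against levels, the gain is negligible at about 0.2 (variance 4% lower) and material from about 0.5 (25% lower at 0.5, 49% lower at 0.7). Against unadjusted change, the gain is large at low r and shrinks as r rises (variance ratio 0.96/1.60 = 0.60 at r = 0.2, and 0.51/0.60 = 0.85 at r = 0.7). The comparison assumes equal SDs at the two times and baseline biopsies that are run on the arrays. The effect is confined to a secondary endpoint, and the primary NFκB analysis is untouched.

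**What to change.** 1. **Secondary objectives, item 1:** define the gene-expression endpoint, like the endpoints beside it, as the change in log expression from the baseline to the 12-month biopsy at the same colon site.
2. **Secondary analyses:** for all three tiers, model 12-month log expression on aspirin, metformin and their interaction, with same-site baseline log expression as covariate. Age and gender may stay. With baseline in the model, the treatment estimates are the same whether the response is the 12-month value or the change, so this agrees with step 1.
3. **Effect measure:** report fold change as the baseline-adjusted ratio between arms.
4. **Platform:** correct the assay named in the sentence on changes, or state which other measurement it concerns.

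**Cost.** This is a wording change and one extra covariate per gene, with no new patients, visits or biopsies. Patients without a usable baseline array drop out of this secondary analysis unless an imputation rule is stated. The fix presumes that baseline biopsies are also run on the arrays. The available text does not confirm this, so the sponsor should check it first.
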